### Outcome variables

A renal event is defined by a >50% decrease in eGFR from the baseline values, doubling of serum creatinine, or ESRD. The estimated GFR for defining renal outcome will be based on the four-variable MDRD formula. However, the Chronic Kidney Disease Epidemiology Collaboration (CKD-EPI) creatinine equation [14] or the CKD-EPI creatinine-cystatin C equation [15] will also be employed to estimate GFR.

At each visit, the subjects will be queried and evaluated for CV events, including myocardial infarction (fatal and nonfatal), coronary revascularization, stroke and new onset or aggravation of congestive heart failure. The causes of death will be verified and classified as cardiac, non-cardiac and unknown. An independent committee will adjudicate all of the primary outcomes. The subjects who withdraw from the study will be traced for this type of information with the help of the National Health Insurance System and Korea Statistical Information Service. The secondary outcomes are hospitalization, fracture, QOL, and economic status during the follow-up.

### Biospecimen collection

Using an EDTA tube, 3 ml of whole blood will be obtained and sent immediately for extracting DNA to the central laboratory. Another 10 ml of whole blood will be obtained using the serum separation tube (SST) and centrifuged within 1 hour for serum separation and sent to the central laboratory for measurements of creatinine, cystatin C, intact parathyroid hormone (iPTH), 25-hydroxyvitamine D3 (25D), 1,25-dihydroxyvitamin D3 (1,25D), and troponin T. Serum creatinine will be measured using an IDMS-traceable method; and cystatin C will be calculated using immunonephelometry calibrated against the reference material [15-17]. The first-voided urine samples (15 ml) will be collected for assaying albumin, protein, calcium (Ca), phosphorus (P), urea, uric acid, electrolytes and osmolality at the central laboratory. The aliquots of the remaining serum and urine samples will be stored in a deep freezer (−70°C) in two different places for future studies. Stringent rules for the sample harvest and processing will be applied to ensure accurate assays. Blood and urine sampling will be conducted under strict monitoring guidelines throughout the study period.

### Follow-up

The participating subjects will visit the center according to the follow-up schedule. At each visit, the subjects will undergo scheduled tests; the investigators will review the subjects’ recent medical histories and occurrence of events. We assumed that 10% of the individuals would withdraw from the study and that ESRD or death would develop subsequently in 10% of the subjects annually [18]. Efforts will be made to prevent drop-outs, i.e., providing free medical examinations, frequent telephone calls and dietary education.

### **Institutional review board** (**IRB) approval**

The study protocol was approved by the IRB at each participating clinical center in 2011.

### Statistical power estimation

With an overall sample size of 600 subjects, which is the size of the each subgroup (GN, DN, HTN, and PKD), 80% power is achieved to detect hazard ratios of approximately 2.00 and 1.60 for an exposure with prevalence of 0.1 and 0.5 and a dropout rate of 10%.

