**Methods/Design:**

Nine nephrology centers in major university hospitals throughout Korea will enroll approximately 2,450 adults with chronic kidney disease over a 5-year period from 2011 to 2015. The participating individuals will be monitored for approximately 10 years until death or until end-stage renal disease occurs. The subjects will be classified into subgroups based on the following specific causes of chronic kidney disease: glomerulonephritis, diabetic nephropathy, hypertensive nephropathy, polycystic kidney disease, and others. The eligible subjects will be evaluated at baseline for socio-demographic information, detailed personal/family history, office BP, quality of life, and health behaviors. After enrollment in the study, thorough assessments, including laboratory tests, cardiac evaluation and radiologic imaging, will be performed according to the standardized protocol. The biospecimen samples will be collected regularly. A renal event is defined by >50% decrease in estimated GFR (eGFR) from the baseline values, doubling of serum creatinine, or end-stage renal disease. The primary composite outcome consists of renal events, cardiovascular events, and death. As of September 2013, 1,470 adult chronic kidney disease subjects were enrolled in the study, including 543 subjects with glomerulonephritis, 317 with diabetic nephropathy, 294 with hypertensive nephropathy and 249 with polycystic kidney disease.

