### Study population

Each participating center will enroll approximately 250 consecutive individuals over a 5-year period from 2011 until 2015, totaling 2,450 adult patients with CKD who provide written informed consent. The participating individuals will be monitored for approximately 10 years until death or until ESRD occurs.

The KNOW-CKD will enroll ethnic Korean patients with CKD who range in age between 20 years and 75 years. The CKD stages from 1 to 5 (predialysis), based on the eGFR, is calculated using the four-variable Modification of Diet in Renal Disease (MDRD) equation as follows:

eGFR (ml/min per 1.73 m^2^) = 175 × [serum Cr (mg/dl)] ^-1.154^ × [age]^-0.203^ × [0.742 if female] × [1.212 if black], using serum creatinine concentrations measured at a central laboratory and an assay traceable to the international reference material [12].

Excluded subjects are those who 1) are unable or unwilling to give written consent, 2) have previously received chronic dialysis or organ transplantation, 3) have heart failure (NYHA class 3 or 4) or liver cirrhosis (Child-Pugh class 2 or 3), 4) have a past or current history of malignancy, 5) are currently pregnant, or 6) have a single kidney due to trauma or kidney donation.

We defined and allocated the specific causes of the CKD into four subgroups: glomerulonephritis (GN), diabetic nephropathy (DN), hypertensive nephropathy (HTN), and polycystic kidney disease (PKD). The definition of the subgroup is defined by the pathologic diagnosis, in the event that the biopsy result is available. Otherwise, the subgroup classification depends on the clinical diagnosis. GN is defined by the presence of glomerular hematuria or albuminuria with or without an underlying systemic disease causing glomerulonephritis. The diagnosis of DN is based on albuminuria in a subject with type 2 diabetes mellitus and the presence of diabetic retinopathy. HTN is defined by the patient’s hypertension history and the absence of a systemic illness associated with renal damage. Unified ultrasound criteria [13] will be used to diagnose PKD. The other causative diseases will be categorized as ‘unclassified’.

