### Results on interim analysis

From July 2011 to September 2013, we enrolled 1,470 participants, including 543 GN, 317 DN, 294 HTN, 249 PKD sub-participants and remaining participants with unclassified subtypes. The baseline demographics and the laboratory values of KNOW-CKD are summarized in Tables 2 and 3. The mean age of the total CKD cohort at the time of study enrollment is 53.6 ± 12.3 years, 38.7% are female, and 31.6% diabetic. The proportion of each CKD stage is as follows; 10.9% (stage 1), 17.2% (stage 2), 18.2% (stage 3a), 22.3% (stage 3b), 23.7% (stage 4) and 7.6% (stage 5, nondialyzed). GN, DN, HTN and PKD were the most common causative diseases in descending order. At baseline, 7.3% of the cohort had a history of coronary heart disease, 8.5% had cerebrovascular disease, and 90.6% had hypertension. In terms of the Charlson comorbidity score and various cardiac parameters, the DN subgroup exhibited the worst profiles (Figure 1 and Table 2). In subjects with advanced CKD stages, the elevated levels of pulse pressure, serum phosphorus, and intact PTH were more pronounced than the subjects with early stages. Hemoglobin levels, 25D and 1,25D, were significantly lower and the left ventricular mass index (LVMI), coronary calcium score and valve calcification were higher in subjects with advanced CKD stages.

**Table 2 T2:** General characteristics of study subjects participating in KNOW-CKD from 2011 to September, 2013

	**Total cohort**^**1**^	**Subcohort**				
		**GN**	**DN**	**HTN**	**PKD**	**p-value**^**2**^
Total participants from 2011 to 2013	**1470**	**543**	**317**	**294**	**249**	
Age	53.6 ± 12.3	50 ± 12.3	59.2 ± 9.3	59.6 ± 10.9	46.9 ± 10.4	< 0.001
Female	569 (38.7)	228 (42)	104 (32.8)	82 (27.9)	127 (51)	< 0.001
BMI (kg/m^2^)	24.4 ± 3.4	24.2 ± 3.4	25.2 ± 3.2	24.8 ± 3.5	23.5 ± 3.1	< 0.001
Waist-Hip ratio	0.89 ± 0.07	0.88 ± 0.07	0.92 ± 0.05	0.9 ± 0.07	0.88 ± 0.06	< 0.001
SBP (mmHg)	127.7 ± 16.5	123.2 ± 14.9	135.8 ± 18.7	127 ± 16.4	128 ± 13.5	< 0.001
DBP (mmHg)	76.6 ± 11.1	75.2 ± 10.6	76.1 ± 11.8	76.8 ± 11.6	79.8 ± 10.2	< 0.001
Pulse Pressure (mmHg)	51.1 ± 12.1	48 ± 10.6	59.7 ± 12.9	50.2 ± 11.5	48.2 ± 9.5	< 0.001
CKD stage 1	160 (10.9)	81 (14.9)	4 (1.3)	2 (0.7)	63 (25.3)	< 0.001
2	253 (17.2)	117 (21.5)	18 (5.7)	18 (6.1)	79 (31.7)	
3a	268 (18.2)	111 (20.4)	45 (14.2)	67 (22.8)	35 (14.1)	
3b	328 (22.3)	110 (20.3)	83 (26.2)	91 (31)	30 (12)	
4	349 (23.7)	93 (17.1)	121 (38.2)	95 (32.3)	30 (12)	
5	112 (7.6)	31 (5.7)	46 (14.5)	21 (7.1)	12 (4.8)	

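### The 80% power figure assumes 600 patients in every cause subgroup, but consecutive enrolment at the observed mix projects to fewer in DN, HTN and PKD, so it does not carry over to them under its own assumptions

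*Protocol article*

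**What the plan says.** Under Statistical power estimation, the article states "With an overall sample size of 600 subjects, which is the size of the each subgroup (GN, DN, HTN, and PKD), 80% power is achieved", the targets being "hazard ratios of approximately 2.00 and 1.60 for an exposure with prevalence of 0.1 and 0.5 and a dropout rate of 10" percent. It gives no event rate, follow-up horizon or alpha there.

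Under Study population, "Each participating center will enroll approximately 250 consecutive individuals over a 5-year period from 2011 until 2015, totaling 2,450 adult patients with CKD". No target by cause is given, and patients outside the four causes stay in the cohort: "The other causative diseases will be categorized as ‘unclassified". The abstract puts the number of centres at nine and the total at approximately 2,450.

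Under Results on interim analysis, "we enrolled 1,470 participants, including 543 GN, 317 DN, 294 HTN, 249 PKD sub-participants and remaining participants with unclassified subtypes".

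Statistical methods and plan has exposure effects estimated within each cause group as well as overall. The only event rate in the article is under Follow-up: "ESRD or death would develop subsequently in 10% of the subjects annually". It is not linked to the power figure.

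**The concern.** The power section presents 600 as the size of each of four subgroups. The recruitment rule does nothing to produce equal subgroups, and the interim counts show that they are not equal: GN is more than twice the size of PKD.

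Differences by cause are the cohort's founding hypothesis, and this is the article's only power statement. A reader who later sees a null exposure effect within PKD could take it as coming from an analysis with 80% power at a hazard ratio of 2.00 or 1.60, when the expected PKD group is about two thirds of the size on which that figure rests.

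**Working it through.** **Inputs.** 600 per subgroup, 80% power, HR 2.00 at prevalence 0.1, HR 1.60 at prevalence 0.5 and 10% dropout (Statistical power estimation); total 2,450 and about 250 per centre (Study population); nine centres (abstract); 543/317/294/249 of 1,470 (Results on interim analysis). Assumed: two-sided 5%, and dropout of 10% in total.

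**1. The plan's own figure.** Schoenfeld: events = (1.960 + 0.842)² / [p(1−p)(ln HR)²].
- HR 2.00, p = 0.1: 7.849 / (0.09 × 0.4805) = 181.5 events
- HR 1.60, p = 0.5: 7.849 / (0.25 × 0.2209) = 142.1 events

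Against 600 × 0.9 = 540 retained, these are 34% and 26%. The event rate is not stated, so the figure cannot be reproduced from the article alone. It is credible, though: a two-proportion calculation with n = 600 and an assumed 20% event risk in the unexposed gives 78.3% and 81.1%. I therefore take 80% at 600 as given.

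**2. Projected sizes.** Unclassified: 1,470 − (543 + 317 + 294 + 249) = 67. Each count is multiplied by 2,450/1,470 = 1.667: GN 905, DN 528, HTN 490, PKD 415, unclassified 112. At this mix, 600 would need a total of 600 × 1,470/317 = 2,782 for DN, 3,000 for HTN and 3,542 for PKD.

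**3. Power and detectable HR at those sizes.** With the same event fraction in every cause, events scale with n. Then power = Φ(2.802 × √(n/600) − 1.960), and the detectable ln HR is the stated ln HR × √(600/n).

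| Subgroup | n | Power at stated HRs | Detectable HR (p = 0.1 / 0.5) | Event fraction needed for 80%, relative to assumed (600/n) |
|---|---|---|---|---|
| GN | 905 | 93% | 1.76 / 1.47 | 0.66 |
| DN | 528 | 75% | 2.09 / 1.65 | 1.14 |
| HTN | 490 | 72% | 2.15 / 1.68 | 1.22 |
| PKD | 415 | 64% | 2.30 / 1.76 | 1.45 |

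The two-proportion method (20% unexposed risk, n not reduced for dropout) gives DN 74%/76%, HTN 71%/73% and PKD 64%/66% for the two HRs, so the result does not hang on Schoenfeld's formula.

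**4. Dependence on the event rate.** Suppose the 10% per year under Follow-up applied to everyone retained.
- 600 subjects, 3 years: 540 × (1 − 0.9³) = 146 events; 4 years: 540 × (1 − 0.9⁴) = 186. This spans the 142 to 182 events needed in step 1.
- PKD, 4 years: 415 × 0.9 × (1 − 0.9⁴) = 128 events, power 65% (HR 2.00) and 76% (HR 1.60).
- PKD, 10 years: 415 × 0.9 × (1 − 0.9¹⁰) = 243 events, power 90% and 96%. On that basis 600 subjects would give 352 events and detect about 1.65 and 1.35, which is better than the article claims.

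**5. Centre target.** 9 × 250 = 2,250, against a stated 2,450; 2,450/9 = 272.

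**The case against.** The strongest reply is that the direction of the error is not settled for each subgroup. The percentages in step 3 assume equal event fractions, while Table 2 shows unequal severity. Stages 4 and 5 make up 167/317 = 53% of DN and 116/294 = 39% of HTN, against 124/543 = 23% of GN. Mean MDRD eGFR is 32.7 in DN and 36.6 in HTN, against 54.9 in GN. Modestly higher event fractions would bring DN and HTN back to 80%. That stands. The argument runs the other way for PKD, where mean eGFR is 67 and 142/249 = 57% are in stage 1 or 2.

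Three stronger readings are tempting, and the article does not support them.
- **The stated hazard ratios clash with 10% events per year.** They do so only if that rate runs for 10 years. The power section gives no horizon, and 3 to 4 years fits. The rate also covers ESRD or death, not the full primary composite.
- **600 in all four is already out of reach.** Filling every group needs 57 + 283 + 306 + 351 = 997 more patients, with 2,450 − 1,470 = 980 places left. That gap of 17 is 0.7% of a total that the abstract calls approximate. Consecutive enrolment at the observed mix is the better evidence.
- **Remaining places should be reserved by cause.** This would give up consecutive enrolment. It is a design trade-off, not a correction.

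It is also fair that an article may leave the event rate and alpha to the full protocol, and that this is an observational cohort with no single confirmatory subgroup test. Neither point covers the size of 600, which the article states outright and its own enrolment figures do not bear out.

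**Conclusion.** The point holds in conditional form. The stated size of 600 per subgroup does not match the enrolment rule or the observed mix: the projections are about 12% (DN), 18% (HTN) and 31% (PKD) below it, and GN is about 51% above. The 80% attached to 600 therefore does not carry over to DN, HTN or PKD under the power statement's own assumptions.

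The loss in power, to about 75%, 72% and 64%, rests on the interim mix persisting, on equal event fractions across causes and on a two-sided 5% test. It is uncertain for DN and HTN and clearest for PKD. A reader might infer that these subgroups are shown to be underpowered. They are not, because with enough follow-up at 10% per year even PKD would reach about 90% or more. The statement needs correcting, but nothing here undermines the cohort itself. The mismatch between 2,250 and 2,450 is a separate, minor inconsistency between rounded figures.

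**What to change.** Delete the clause that gives 600 as the size of every cause subgroup. In its place, report power or detectable hazard ratios at each subgroup's projected size (about 905, 528, 490 and 415), stating for each the assumed event rate by cause, the follow-up horizon and the expected event count, and give alpha and sidedness once. Use separate event rates by cause, since baseline kidney function differs so much between PKD and DN.

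Reconcile the centre target with the total: about 272 per centre for 2,450, or 2,250 if about 250 per centre is what was meant.

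The cost is a recalculation and a few lines of text. Enrolment, follow-up and analyses do not change. With equal event fractions, the published detectable hazard ratios become less favourable for three subgroups and more favourable for GN; with cause-specific rates, DN and HTN may stay close to the present figures.

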### Statistical methods and plan

The baseline characteristics of the study participants for each subgroup were presented with descriptive statistics using a one-way analysis of variance or Kruskal-Wallis test according to the distribution of continuous variables and a chi-square test or Fisher’s exact test for categorical variables.

To analyze the association of outcome variables, the time-to-event analysis will be used to evaluate primary outcomes, such as renal events (initiation of renal replacement therapy and 50% decline of GFR), CV events (myocardial infarction and ischemic stroke) and death. The Kaplan-Meier curves and the proportional hazard models will serve as major statistical methods for the outcomes. The incidence or mortality rates according to each outcome variable will be calculated for each etiologic group; the incidence ratios will be presented with reference to the diabetic nephropathy subgroup. The effect of exposure on the development of outcomes will be analyzed separately in each group and in the overall groups. The heterogeneity of each relative risk within the KNOW-CKD subcohort will be analyzed using the Cochran Q test or using a shared-frailty model, where time-dependent confounders should be adjusted [19]. The CKD progression will be evaluated using decreased GFR calculations. Because it is common for a patient with CKD to have a non-linear decline in GFR or a prolonged period of non-progression [20], we will assess the longitudinal trajectory of GFR for the individual participants of KNOW-CKD using the Bayesian smoothing technique [21]. If the progression of CKD is steady and linear, the generalized estimating equation will be adopted to compare the slope of the GFR with repeated measurements. The progression of CKD will be supplemented with an event-based analysis, whereby the occurrence of ESRD or the substantial decrease of GFR will be treated as the events of interest.

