## Background

Chronic kidney disease (CKD) is a rapidly growing disease worldwide. The prevalence of CKD in Korea is estimated to be 13% in the adult population [1]. Approximately 5% of the Korean adult population is estimated to have decreased renal function with an estimated glomerular filtration rate (eGFR) less than 60 ml/min per 1.73 m^2^[1]. CKD, which leads to dialysis or kidney transplantation, presents a major threat to cardiovascular (CV) events and all-cause mortality [2,3]. A patient with CKD is more likely to die of CV disease than to start renal replacement therapy.

Since 2002, a large number of epidemiologic studies, in addition to the general population, have demonstrated a significantly increased risk of adverse consequences in subjects with albuminuria, even in the presence of normal or mildly decreased GFR [4,5]. This finding warrants a broader view of the early stages of CKD within the nephrology population to determine the variables associated with CKD and the increased risks of death and adverse outcomes [6]. However, the mechanistic link between albuminuria and adverse consequences has not been established.

Kidney Disease: Improving Global Outcomes (KDIGO) 2012 Clinical Practice Guideline for the Evaluation and Management of CKD recommends a new classification of CKD, based on the cause, GFR category, and albuminuria (CGA) [7]. The characteristics of CKD differ significantly depending on the underlying disease or the location of the pathologic-anatomic abnormalities. Therefore, we hypothesized that the progression and complications of CKD should be different among the disease subgroups, which cause CKD. A new perspective in the viewpoint of the “CGA” paradigm is required to analyze and interpret the various parameters associated with CKD.

Nevertheless, recently established CKD cohort studies [8-11] are primarily based on the CKD population with low GFR (less than 60 ml/min per 1.73 m^2^). The above studies targeted the cardiovascular complications from subjects with moderate or severe renal impairment. In these studies, the early stages of renal injury are excluded from their target population and the specific causes of CKD are not considered. In contrast, a new CKD cohort study, including all of the stages of the pre-dialysis CKD population and considering the specific causes of CKD, may lead us to gain insight into understanding the natural progression of CKD and the association between CKD and CV outcomes or mortality.

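### A standard shared-frailty model is offered as an alternative to Cochran Q for heterogeneity of relative risks across causes of CKD, but it measures differences in baseline event rate

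*Protocol article*

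**What the plan says.** All of this is in the Protocol article. Under Statistical methods and plan, exposure effects come first: "The effect of exposure on the development of outcomes will be analyzed separately in each group and in the overall groups". The next sentence is the one at issue: "The heterogeneity of each relative risk within the KNOW-CKD subcohort will be analyzed using the Cochran Q test or using a shared-frailty model". It ends with a rider, "where time-dependent confounders should be adjusted", and a citation.

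Table 2 uses the column heading Subcohort for glomerulonephritis (GN), diabetic nephropathy (DN), hypertensive nephropathy (HTN) and polycystic kidney disease (PKD). These match the Study population section: "We defined and allocated the specific causes of the CKD into four subgroups". The natural reading is therefore a test of whether an exposure's relative risk differs by cause, with two methods offered as alternatives.

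The Background expects outcomes to differ by cause: "we hypothesized that the progression and complications of CKD should be different among the disease subgroups". That is a statement about outcome rates, not about exposure hazard ratios.

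**The concern.** The two methods joined by the word or do not test the same hypothesis. Cochran Q compares exposure effects between groups. A shared frailty in its standard form multiplies each group's baseline hazard and leaves a single exposure effect common to all groups, so equality of the relative risks is assumed rather than tested.

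The stake is interpretation. If the frailty route is taken and its variance is reported as the heterogeneity result, ordinary differences in prognosis between causes would be presented as evidence that a risk factor acts differently by cause. Those differences are already covered by the incidence ratios planned against the DN subgroup.

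**Working it through.** **No plan figure to reproduce.** The article gives no number for this analysis. The check is by model structure, then by simulation.

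**Structure.** For subject j in cause group i:

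h_ij(t) = u_i × h0(t) × exp(β x_ij)

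The term u_i scales the group's baseline hazard. β carries no group index, so there is one hazard ratio, exp(β). With exponential times and gamma frailty of variance θ (k = 1/θ), the log-likelihood is

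a ΣD_i + β ΣD_i1 + Σ[ lnΓ(k + D_i) − lnΓ(k) + D_i ln θ − (k + D_i) ln(1 + θH_i) ]

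Here a is the log of h0, D_i is all events in group i, D_i1 its events among the exposed, and H_i = exp(a) × (T_i0 + exp(β) T_i1), with T_i0 and T_i1 the unexposed and exposed person-time. The exposed events enter only as a total over groups. If they are redistributed between groups while each D_i, the overall exposed total and the person-time stay fixed, the fitted θ does not change, although the group hazard ratios do.

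Cochran Q uses exactly that discarded information: Q = Σ w_i (b_i − b̄)², with b_i the log hazard ratio in group i, w_i = 1/(1/D_i1 + 1/D_i0), b̄ the weighted mean, and 4 − 1 = 3 df.

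**Inputs from the article.**
- Four groups of 600 (Statistical power estimation: "With an overall sample size of 600 subjects, which is the size of the each subgroup (GN, DN, HTN, and PKD").
- Exposure prevalences 0.1 and 0.5, hazard ratio 1.6 and 10% dropout (same section: "80% power is achieved to detect hazard ratios of approximately 2.00 and 1.60 for an exposure with prevalence of 0.1 and 0.5").
- ESRD or death in 10% per year (Follow-up), used only for the order of magnitude of the hazards.
- Baseline differences (Table 2): mean MDRD eGFR 32.7 in DN and 67 in PKD. CKD stages 4 and 5 make up 38.2 + 14.5 = 52.7% of DN and 12 + 4.8 = 16.8% of PKD.

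**Assumptions.** Exponential times, 5 years of follow-up, no covariates, and the hazards and hazard-ratio patterns shown below. There were 400 runs per scenario. The frailty variance was tested by a likelihood ratio against a 50:50 chi-square mixture, and both tests used 0.05.

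| Scenario (groups in a fixed order) | Prevalence | Frailty rejects | Cochran Q rejects |
|---|---|---|---|
| A: HR 1.6 in all; baseline hazards 0.054, 0.12, 0.09, 0.042 per year | 0.5 | 100% | 4.8% |
| A | 0.1 | 100% | 4.5% |
| A2: HR 1.6 in all; baseline hazards within ±15% of 0.08 | 0.5 | 68.8% | 5.2% |
| A2 | 0.1 | 57.8% | 3.5% |
| B: HRs 1.0, 2.2, 1.6, 1.0; group-average hazards equal | 0.5 | 2.0% | 97.8% |
| B | 0.1 | 3.5% | 75.2% |
| C: no difference of either kind | 0.5 | 2.2% | 5.0% |
| D: HRs as in B; unexposed hazards equal at 0.08 | 0.5 | 100% | 99.2% |

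In A the largest and smallest baseline hazards differ by 0.12/0.042 = 2.9-fold.

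D shows why the frailty test sometimes appears to work. At prevalence 0.5 the group-average hazards are 0.08 × (1 + HR)/2, that is 0.08, 0.128, 0.104 and 0.08. The test reacts to those averages. In B the unexposed hazards are set at 0.08 ÷ (1 + HR)/2, that is 0.08, 0.05, 0.0615 and 0.08, so the averages are equal and the signal disappears.

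A separate simulation with other settings (10 years, prevalence 0.3, common HR 1.5, baseline hazards 3 to 9% per year, 300 runs) gave 100% for frailty and 4% for Cochran Q.

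**The case against.** **The specification is not visible.** The article names neither the cluster variable nor the form of the frailty model. The rider on time-dependent confounders suggests that frailty may be meant as the adjusted regression framework, and the cited source is not at hand. This stands as a limit: a model with a random exposure slope or an exposure-by-cause term would answer the question. But the article mentions neither, and covariate adjustment alone supplies neither. The point concerns a method the article names for a purpose, not a detail left to a fuller document.

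**Relative risk might mean the incidence ratios against DN.** Differences in event rate would then be a legitimate target. The wording does not rule this out, but the sentence directly before concerns exposure effects by group and overall, which favours the other reading.

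**Real effect modification would still be seen.** This largely stands. Group-specific exposure effects are planned whichever method is used, so a reader might infer that the frailty option would hide effect modification altogether, and the article does not support that. The miss in scenario B also needs group-average hazards to be equal, which is unlikely when baseline risk differs by cause.

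**The frailty test is not always wrong.** A reader might infer from scenarios A and B that it always misleads. Scenario D shows otherwise, although there it rejects because average hazards differ.

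**Conclusion.** The point holds for the shared-frailty option only. Cochran Q is valid and is named first, so it would be wrong to infer that the article's whole approach to heterogeneity is unsound. What is wrong as written is offering the two methods as interchangeable.

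The realistic harm is a false signal. With equal hazard ratios, the frailty test rejected in 58 to 100% of runs, depending on how far the baseline hazards differed, against 3.5 to 5.2% for Cochran Q. Missed effect modification is possible but secondary. A variance estimated from only four groups would also be imprecise.

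The direction follows from the model structure, given a random intercept by cause and no exposure-specific term. The rejection rates depend on the assumed hazards, follow-up and hazard-ratio patterns, and are illustrative. No stated sample size or power figure is affected.

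**What to change.** Reword the heterogeneity sentence under Statistical methods and plan along these lines:

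- Heterogeneity of an exposure effect across the four cause subgroups is judged by Cochran Q on the cause-specific log hazard ratios already planned.
- Where time-dependent confounders must be adjusted, it is judged by a likelihood-ratio test of the exposure-by-cause interaction in a Cox model stratified by cause (3 df for four subgroups).
- Shared frailty is kept only to allow for clustering, for example by centre, with the cluster variable named. Otherwise it is explicitly extended with a random exposure slope or an exposure-by-cause term, and that term is what gets tested.

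The cost is a sentence or two in the plan and standard software. No new data and no change in sample size are needed.

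### Comparing GFR slopes by ordinary GEE while eGFR series stop at ESRD or death flattens the estimated decline, most in the cause groups with the lowest baseline eGFR

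*Protocol article*

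**What the plan says.** Statistical methods and plan sets out three strands for GFR progression. Because decline is often non-linear, "we will assess the longitudinal trajectory of GFR for the individual participants of KNOW-CKD using the Bayesian smoothing technique". For the linear case, "If the progression of CKD is steady and linear, the generalized estimating equation will be adopted to compare the slope of the GFR". Then: "The progression of CKD will be supplemented with an event-based analysis", in which ESRD or a large fall in GFR counts as the event.

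Study population fixes when measurement ends: "The participating individuals will be monitored for approximately 10 years until death or until ESRD occurs". Follow-up gives the expected losses: "We assumed that 10% of the individuals would withdraw from the study" (no time unit), and "ESRD or death would develop subsequently in 10% of the subjects annually".

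The section names no weighting, joint model or other link between the slope and the event that ends the series. Under Outcome variables, patients who withdraw are traced for events and causes of death, which does not restore their eGFR values.

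**The concern.** Unweighted GEE is in general consistent only if the chance of still being measured does not depend on past outcomes. Here it does: reaching ESRD is a consequence of low GFR, and it ends the series. Later visits then over-represent patients who started high or decline slowly, and the fitted average slope flattens.

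The effect need not cancel between groups. Patients who start nearer ESRD are cut off sooner at the same rate of decline, and baseline eGFR differs about two-fold between causes. Describing natural history by cause is among the goals in the Background and is repeated in the Discussion, so the distortion would fall on a contrast the study wants to report.

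**Working it through.** **The plan's own figures.** No figure is stated for the slope analysis. The only power statement concerns hazard ratios ("80% power is achieved to detect hazard ratios of approximately 2.00 and 1.60 for an exposure with prevalence of 0.1 and 0.5") and plays no part here.

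**Retention implied by the article.** At 10% per year for ESRD or death, before withdrawals: 0.9^5 = 0.59 at 5 years and 0.9^10 = 0.35 at 10 years.

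**Unequal exposure to truncation (Table 2).**

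| | DN | HTN | GN | PKD |
|---|---|---|---|---|
| Baseline MDRD eGFR, mean (SD) | 32.7 (17.9) | 36.6 (17.4) | 54.9 (30.6) | 67 (33.9) |
| Stage 4 + 5, n/N | (121+46)/317 | (95+21)/294 | (93+31)/543 | (30+12)/249 |
| Share | 52.7% | 39.5% | 22.8% | 16.9% |

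**Simulation A: GEE under truncation.** 40,000 patients per group, Table 2 baselines, Table 1 visits (0, 0.5, 1 to 10 years), and a linear trajectory for every patient. Assumptions not in the documents: true mean slope −3 in every group, between-patient slope SD 0 to 3, ESRD at eGFR 10, death 2% per year, measurement SD 4. Without truncation GEE returns −3.0 in every group. With eGFR removed after ESRD or death:

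| Slope SD | Working correlation | DN | HTN | GN | PKD |
|---|---|---|---|---|---|
| 0 | exchangeable | −3.00 | −3.00 | −3.00 | −3.00 |
| 0 | independence | −0.64 | −1.16 | −1.42 | −1.99 |
| 1 | exchangeable | −2.66 | −2.69 | −2.84 | −2.89 |
| 1 | independence | −0.58 | −1.01 | −1.30 | −1.87 |
| 2 | exchangeable | −1.88 | −2.02 | −2.47 | −2.64 |
| 2 | independence | −0.25 | −0.62 | −0.98 | −1.51 |
| 3 | exchangeable | −1.05 | −1.28 | −1.99 | −2.27 |
| 3 | independence | +0.34 | +0.01 | −0.49 | −1.05 |

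Exchangeable GEE is unbiased at SD 0 because its working covariance is then the true one. Varying slopes break that.

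At SD 2 the order of the exchangeable bias (DN, HTN, GN, PKD) is unchanged with ESRD at eGFR 7 (1.00, 0.88, 0.48, 0.32) or 15 (1.29, 1.14, 0.62, 0.43). It also holds with mean slope −2 and SD 1.5 (0.60, 0.50, 0.25, 0.15).

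**Simulation B: GEE beside a mixed model.** True slope −3 in both groups, death 2% per year:

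| Slope SD | Exchangeable GEE, DN | Exchangeable GEE, PKD | Spurious gap |
|---|---|---|---|
| 1 | −2.81 | −2.95 | 0.14 |
| 2 | −2.02 | −2.67 | 0.65 |
| 3 | −1.44 | −2.51 | 1.07 |

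A random intercept-and-slope mixed model gave about −2.9 to −3.1 throughout. Runs with 600 per group and no deaths gave mixed-model slopes between −2.85 and −3.16.

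Across all runs, including simulation A, the spurious DN–PKD gap under exchangeable GEE was 0.12 to 0.23 at SD 1, 0.58 to 0.76 at SD 2 and 0.95 to 1.22 at SD 3.

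**Does the ranking reverse?** With DN truly faster (−4 against −3 in PKD; 600 per group), exchangeable GEE gives:
- SD 1: −3.73 against −2.90, ranking kept.
- SD 2: −3.02 against −2.81, ranking kept with the gap shrunk.
- SD 3: −2.24 against −2.29 to −2.50, a marginal reversal.

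With −4.5 (SD 3) in DN against −3.5 (SD 2) in PKD, simulation A reverses: −2.19 against −3.08 (exchangeable) and −0.09 against −1.71 (independence).

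**The case against.** **GEE is one conditional branch and not the primary analysis.** This stands. Kaplan–Meier and proportional hazards are the main methods, slope is not a listed primary or secondary outcome, and the GEE sentence does not say which groups are compared; the contrast by cause is taken from the goals and the Discussion. The linearity condition is no protection, however: every simulated trajectory was linear.

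**The event analysis and the smoothing cover the gap.** In part. Fast progressors are counted as events, so they are not lost to the study. But a separate event analysis does not correct a slope contrast, and the smoothing is described for individual trajectories.

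**An article leaves details to the SAP.** Working correlation and drop-out weighting are such details, and weighted GEE is still GEE. Their absence is no finding. The point is that the method the article does name, in its ordinary form, does not suit the stopping rule it also states.

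**The size is assumed.** This stands. The documents give no slope mean or SD. At SD 1 the exchangeable bias is modest, and at SD 0 it vanishes. A slope SD of 3 around −3 implies that about 16% of patients have rising GFR. Against this, the article itself expects prolonged non-progression in some patients, which argues for real heterogeneity.

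**The mixed model is favoured by the set-up.** Partly fair: stopping depended on eGFR, with death at most an added constant 2% per year. Death tied to unobserved GFR was not tested, hence the joint model below.

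**Conclusion.** The point holds. Ordinary GEE slopes from series that end at ESRD or death are biased toward no decline, and more so in DN and HTN than in GN and PKD. With equal true slopes of −3, the false DN–PKD difference under exchangeable GEE runs from about 0.1 to 1.2 mL/min/1.73 m² per year as slope SD goes from 1 to 3. Independence GEE is more biased at every SD tried. Direction and ordering held in every setting except exchangeable GEE with identical slopes; the sizes are illustrations under assumed values.

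Three stronger readings should be resisted. A reader might infer that the sickest group will appear to decline least whatever the truth; a reversal occurs only in some settings, and at a true −4 against −3 not under exchangeable GEE at SD 1 or 2. A reader might infer that linearity will be judged on survivors only; the article does not say how it is judged, and patients who reach ESRD contribute data until then, so the text gives no ground for striking the condition as an error. A reader might extend the problem to the primary time-to-event results, where ESRD and death are themselves outcomes; those are not affected.

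**What to change.** For the slope comparison, replace GEE with a linear mixed model for eGFR with random intercept and slope, using a spline in time if decline is non-linear, and take the cause-by-time term as the contrast. Such a model remains valid when stopping depends on observed eGFR, provided its random-effects assumptions are adequate.

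Pre-specify a joint (shared-parameter) model of eGFR and time to ESRD or death as sensitivity analysis, since stopping may also depend on GFR that was not observed, and state how death is handled. GEE may stay as a secondary check.

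The cost is a change of analysis wording, some extra modelling, and reliance on the random-effects assumptions. No new data or visits are needed.
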